### Objectives

The primary objective will be to assess the effectiveness of oral mirtazapine in improving HRQoL in poly-symptomatic advanced cancer patients suffering from depression after 56 days of treatment, compared with oral escitalopram.

The secondary objectives are:

i- To assess the effectiveness of oral mirtazapine in poly-symptomatic advanced cancer patients suffering from depression compared with escitalopram on the following outcomes:The experience of poly-symptomatology, poly-medication, and taking antidepressant agents and explore the dynamic of this experience between inclusion and 56 days.The improvement of the following symptom intensity: depressive mood, pain, nausea, lack of appetite, vomiting, breathlessness, sleep disorders and anxiety at 28 and 56 days.The improvement of the different functional capacities at 56 days.The mitigation of the loss of weight at 28 and 56 days.The use of medications to treat associated symptoms at 28 and 56 days.

ii- To assess the safety of oral mirtazapine in poly-symptomatic advanced cancer patients suffering from depression compared with escitalopram from 7 days.

iii- To assess the compliance to the treatments.

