The proportion of patients having an improvement in the different EORCT-QLQ-C30 functioning scales will be compared between baseline, day 28 and day 56. The following cut-offs will be used for defining significant changes: 3 points for the Cognitive Functioning, 2 points for the Physical functioning, and 6 points for the Emotional Functioning and Role functioning [26, 27]. Financial functioning will not be assessed as the French health care system does not fit with this evaluation (cancer care is free of charge to the patient).

Weight variations will be assessed between baseline, day 28 and day 56.

The use of painkillers will be assessed using the proportion of patients that had stable (± 20%) morphine oral equivalent between baseline, day 28 and day 56. For other symptomatic treatments, the proportion of patients that increased the doses (or had new symptomatic treatment) between baseline, day 28 and day 56 will be assessed.

The security of use will be assessed using the number of new adverse effects reported using the ASEC on day 14, 28 and 56 and compared with baseline. Adverse events will also be recorded and graded using the CTCAE V4.0. The ESAS12-F subscales for drowsiness, fatigue and constipation will be used to compare these symptoms between baseline, day 28 and day 56. A higher degree of intensity will be considered from a 1 point difference [23].

Finally, adherence to medication will be assed using the MARS and Proportion for Days Covered at day 56 [28].

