## Discussion

If mirtazapine is proven to be efficient in improving patients’ quality of life, independently of its antidepressant effect, in advanced cancer poly-symptomatic patients would constitute a major progress. Additionally, this study might highlight target symptoms that could be relieved using mirtazapine and potential target symptom clusters.

This could allow limiting polypharmacy in advanced cancer patients by offering a new therapeutic option well tolerated in this frail population. Additionally, this would mitigate the risk of adverse event and drugs interaction in this population often affected by polypharmacy due to numerous conditions and symptoms. This would constitute a major step for patients’ security. As mirtazapine is a very cheap drug, this would also contribute in limiting health care expenditures.

Besides limiting polypharmacy, several symptoms have very limited therapeutic options currently available. This is the case for cancer anorexia. Few drugs, including megestrol acetate and corticoids, have been proven to be effective in improving appetite. However, they have important side effects, limiting their use in the overall advanced cancer population. As mirtazapine is expected to be well tolerated, any effectiveness sin improving appetite might open an interesting therapeutic way for anorexia in advanced cancer.

For breathlessness treatment, no drug is currently licensed in the European Union. Morphine has been evaluated many times, but its effectiveness is still under debate. King’s College London recently launched an ambitious project aiming to assess the effectiveness of mirtazapine in alleviating breathlessness in chronic lung disease [32]. Results from this wide UK randomized control trial and form our study could motivate considering licensing mirtazapine in treating this symptom.

Additionally, mirtazapine is available in many countries under the shape of orodispersible tablets. This galenic form ensures its use for most cancer patients, including those who have swallowing disorders, intestinal obstruction or any other contraindication for oral intakes, while limiting venous access when not necessary.

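### The opioid outcome is non-directional: a fall of more than 20% in morphine equivalent is scored the same as a rise of more than 20%, which can dilute a real difference between arms

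*Protocol article*

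**What the plan says.** The Objectives section lists, among the secondary effectiveness objectives, "The use of medications to treat associated symptoms at 28 and 56 days". Outcomes assessment turns this into two measures.

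- **Opioids:** "The use of painkillers will be assessed using the proportion of patients that had stable". The quantity meant is the oral morphine equivalent, followed from baseline to days 28 and 56 with a tolerance of 20%. The tolerance carries a ± sign, so the band is two-sided. No other part of the article reports decreases and increases in opioid dose separately.
- **All other symptomatic drugs:** "the proportion of patients that increased the doses (or had new symptomatic treatment) between baseline, day 28 and day 56 will be assessed". This rule has a direction: only an increase or a new drug counts as an event.

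Pain is also a target symptom in its own right. The Objectives include "The improvement of the following symptom intensity: depressive mood, pain, nausea, lack of appetite" and further symptoms, and pain intensity is measured by the ESAS-12F. The Discussion gives the wider motive: "This could allow limiting polypharmacy in advanced cancer patients by offering a new therapeutic option".

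**The concern.** The opioid measure sits among the effectiveness outcomes, so a reader will want to know which arm used less or more opioid. The proportion stable cannot say. A patient at −30% and a patient at +30% are both non-stable, although the first may reflect better pain control and the second worse. The neighbouring rule does not have this problem. A patient who reduces another symptomatic drug is counted with those who did not increase, whereas a patient who cuts morphine by 30% is counted with those who escalated.

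At stake is the interpretation of one secondary result. A real difference in opioid escalation could be reported as smaller than it is. In less likely circumstances it could appear as no difference, or point the other way.

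**Working it through.** **The plan's own figures.** The article gives no expected rate, effect size or power for the opioid outcome, so there is nothing specific to reproduce. The trial size reproduces and serves only as context. The SD of change is √(26² + 26² − 2 × 0.5 × 26 × 26) = 26. A difference of 8 points at two-sided alpha 0.05 and 80% power needs 166 per arm (stated: 167). Then 167 / 0.8 = 208.75, rounded up to 209 per arm, or 418 in total, as stated.

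**Algebra of the definition.** In each arm let D be the proportion falling by more than 20% and I the proportion rising by more than 20%. Then

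stable = 1 − D − I.

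For mirtazapine (M) minus escitalopram (E),

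difference in stable = (I_E − I_M) − (D_M − D_E) = a − b,

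where a is the reduction in increases and b is the gain in decreases. For a > 0:

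- b = 0: the difference is a, and nothing is lost.
- 0 < b < a: the difference is diluted but keeps its direction.
- b = a: the difference is zero.
- b > a: the sign reverses.

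This follows from the definition alone. Only the size depends on the rates.

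**Illustrations.** All shares below are assumed. They are given as percentages in the order decrease / within band / increase, with 167 per arm and a two-sided 0.05 test of two proportions. The comparison measure is the proportion with no increase above 20%.

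| Escitalopram | Mirtazapine | a | b | Difference in stable (a − b) | Power, stable | No increase, E vs M | Power, no increase |
|---|---|---|---|---|---|---|---|
| 10/50/40 | 10/60/30 | 10 | 0 | +10 | about 45% | 60% vs 70% | about 48% |
| 10/50/40 | 15/55/30 | 10 | 5 | +5 | about 15% | 60% vs 70% | about 48% |
| 10/50/40 | 20/50/30 | 10 | 10 | 0 | alpha level only | 60% vs 70% | about 48% |
| 10/50/40 | 30/50/20 | 20 | 20 | 0 | alpha level only | 60% vs 80% | about 98% |
| 10/50/40 | 30/45/25 | 15 | 20 | −5 | about 15%, wrong direction | 60% vs 75% | about 84% |
| 10/65/25 | 20/65/15 | 10 | 10 | 0 | alpha level only | 75% vs 85% | about 63% |

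The first row shows that the two measures perform almost alike when there is no shift into decreases. The second shows dilution from a modest shift: half of the 10-point effect disappears. The remaining rows need b to be at least as large as a.

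**The case against.** **The rates are invented.** This stands. Cancellation and reversal appear only because the assumed gain in decreases matches or exceeds the assumed reduction in increases. Nothing in the article suggests that this will happen over 56 days in patients with advanced cancer. If few patients reduce their opioid by more than 20%, little is lost.

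**Opioid reduction is not a stated aim.** This largely stands. A reader might infer that the trial expects opioid sparing and so scores its own hoped-for benefit as a failure. The objective is worded neutrally, the polypharmacy argument concerns one drug serving several symptoms, and no section predicts a lower opioid dose. A stability measure could also be meant as background to the ESAS pain score, although the article does not link the two and presents it as the measure of painkiller use.

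**Different rules for different drugs are a design choice.** This stands in part. The two sentences cover different drug groups and do not contradict each other. They still give one objective a directional and a non-directional measure, without a reason.

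**Patients with no opioid at baseline.** A reader might infer that the band breaks down for them, since 20% of zero is zero. It does not: a patient who stays at zero is unchanged, and any new start falls outside the band.

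**The article is condensed.** Reporting the proportion stable does not prevent a breakdown by direction elsewhere. But the measure, its threshold and its two-sidedness are all stated here, so the point concerns what is fixed and not what is left out.

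**Conclusion.** The point holds in a limited form. As defined, the opioid outcome does not distinguish a reduction of more than 20% from an increase of more than 20%. It can therefore dilute a real between-arm difference in opioid use. It cancels or reverses that difference only if the between-arm gain in decreases equals or exceeds the reduction in increases. The loss ranges from almost none (45% against 48% power in the first row of the table) to complete, and the documents contain no opioid rates that would place the trial within that range.

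It would go too far to say that the secondary objective on medication use is defeated. The directional measure for other symptomatic drugs serves the same objective, polymedication is explored in the interviews, and pain is measured separately. None of these recovers the direction of opioid change, but they confine the damage to one component of one secondary objective. The primary outcome and the sample size are untouched.

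**What to change.** Define the opioid outcome as three ordered categories of change in oral morphine equivalent from baseline, at day 28 and at day 56: decreased by more than 20%; within ± 20% (including patients who remain without an opioid); increased by more than 20% or newly started. Compare the arms on the ordered outcome and show the share in each category by arm. Report alongside it the proportion increased or newly started, to match the rule for other symptomatic treatments. That proportion should not stand alone, because it merges decreases with no change and would still hide reductions.

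No new data are needed: Table 1 already schedules the treatment list at J0, J28 and J56, and the present outcome needs the same doses. The cost is an amended secondary outcome definition in a protocol that already has ethics approval. The change should be made before outcome data are examined by arm. It alters how opioid use is summarised and no treatment rule.

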### Sample Size

Based on an expected standard deviation of 26 in our primary outcome (The Global health Status), and considering a correlation of 0.5 between inclusion and day 56 (corresponding in a standard deviation of the variation of the GHS score of 26 between baseline and day 56), and expecting a moderately clinically significant difference of 8 points between groups, it will be necessary to include 418 participants (bilateral test, alpha risk of 0.05, power of 0.8, attrition 0.2).

Considering the risk of lost to follow-up due to our population global condition, we considered an attrition rate of 20% when calculate the sample size.

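### The painkiller outcome counts only a stable (±20%) opioid dose, so it cannot tell opioid sparing from opioid escalation and can weaken, cancel or sometimes reverse a real difference between arms

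*Protocol article*

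**What the plan says.** Under Outcomes assessment, painkiller use is measured by the "proportion of patients that had stable (± 20%) morphine oral equivalent between baseline, day 28 and day 56". The article gives no other painkiller-dose measure, no separate class for a decrease, and no statement of which direction is favourable.

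The next sentence handles all other symptomatic treatments differently, by "the proportion of patients that increased the doses (or had new symptomatic treatment) between baseline, day 28 and day 56". That rule has a direction.

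Both measures serve the secondary objective worded as "The use of medications to treat associated symptoms at 28 and 56 days". The Objectives section lists it under the effectiveness of mirtazapine compared with escitalopram. Pain is among the symptoms whose improvement is a secondary objective: "depressive mood, pain, nausea, lack of appetite, vomiting, breathlessness, sleep disorders and anxiety at 28 and 56 days". On the expected benefit, the Discussion says: "This could allow limiting polypharmacy in advanced cancer patients".

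**The concern.** A patient with a baseline opioid dose falls into one of two classes: within 20% of that dose, or outside it. A patient whose dose drops by a third and one whose dose rises by a third share a class. Pain is a target symptom and medication use is an effectiveness objective, so these two patients should not be treated alike. The outcome is also out of line with the directional rule beside it.

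At stake is the reading of one secondary comparison. A lower stable proportion with mirtazapine could mean more escalation or more sparing, and the stated measure does not say which. Equal proportions could hide a real shift from rises to falls.

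**Working it through.** **The plan's own figures.** The protocol gives no rate, sample size or power for the painkiller outcome. Its only relevant number is the evaluable size for the primary outcome, 167 per group (Statistics), used below for scale. It reproduces:

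- SD of change = √(2 × 26² × (1 − 0.5)) = 26.
- n per arm = 2 × (1.960 + 0.842)² × 26² / 8² ≈ 166, against 167 stated.
- Total with 20% attrition = 2 × 167 / 0.8 = 417.5, so 418 as stated.

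**The logic, which needs no outside figure.** Let F, S and R be the proportions with a fall of more than 20%, within ±20%, and a rise of more than 20%. Then S = 1 − F − R, and between arms ΔS = −(ΔF + ΔR). If a drug reduces rises and increases falls, the two changes offset each other in ΔS. The stable proportion favours that drug only if the reduction in rises exceeds the gain in falls.

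**Three-class illustration.** Assumed comparator F/S/R = 10/50/40%. Differences are in percentage points, drug minus comparator.

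| Assumed drug arm F/S/R | Shift | Δ stable | Δ no rise >20% |
|---|---|---|---|
| 20/40/40 | stable to fall | −10 | 0 |
| 10/40/50 | stable to rise | −10 | −10 |
| 20/50/30 | rise to fall | 0 | +10 |
| 30/40/30 | 20 more falls, 10 fewer rises | −10 | +10 |
| 10/60/30 | rise to stable | +10 | +10 |

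The first two rows are opposite effects with the same result on the stated outcome. Row three cancels, row four reverses and row five keeps the right direction. In row one the no-rise proportion also shows nothing, so it cannot replace a three-class comparison.

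**Lognormal dose-ratio illustration.** The ratio of follow-up to baseline dose is lognormal, with cut-offs at 0.8 and 1.2 and an assumed log-SD of 0.3 to 0.5.

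| Mean log ratio, comparator v drug | Δ stable | Δ no rise >20% |
|---|---|---|
| 0 v −0.2 or −0.3 | −1.8 to −15.5 | +13.5 to +21.8 |
| +0.1 v −0.1 | +0.5 to +1.9 | +14.8 to +21.9 |
| +0.3 v +0.1 | +4.7 to +16.1 | +15.8 to +26.1 |

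First row: the drug lowers the median dose by 1 − e^−0.2 = 18% to 1 − e^−0.3 = 26%, and the stable proportion points against it. Second row: the difference nearly vanishes. Third row: comparator doses mostly rise, and the direction is right but weaker.

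**What a test could show.** Two-proportion z-tests with pooled variance, 167 per arm, assuming that every patient takes an opioid at baseline:

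- (a) Drug 20/55/25, comparator 10/55/35. Stable is 55% v 55%. For rises, z = (0.25 − 0.35)/√(0.30 × 0.70 × 2/167) = −1.99, p = 0.046.
- (b) Drug 30/45/25, comparator 10/60/30. For stable, z = (0.45 − 0.60)/√(0.525 × 0.475 × 2/167) = −2.74, p = 0.006 against the drug, although it has fewer rises. For falls, z = (0.30 − 0.10)/√(0.20 × 0.80 × 2/167) = 4.57.

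Table 2 requires neither pain nor opioid use. If only 100 per arm took an opioid (also an assumption), p would be about 0.12 for the rises in (a) and about 0.03 for the stable contrast in (b). The misclassification is the same; only the p-values move.

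**The case against.** A reader might infer that the definition turns a benefit into a harm as a matter of course, or that the comparison cannot be interpreted at all. The documents do not support either. The Background says symptom burden worsens as disease progresses, and the trial enrols patients with incurable cancer, so most unstable doses may be rising ones. Then the stable proportion keeps the right sign, only weakened. This stands as a limit on the point. It does not remove it, because the protocol gives no opioid trajectories from which the sponsor could show that this setting applies.

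It can also be said that a lower opioid dose is nowhere named as a success. The objective is worded neutrally, and limiting polypharmacy concerns the number of drugs more than the dose of one. That is fair: the favourable direction is inferred from pain being a target symptom and from the objective sitting under effectiveness. The failure to separate falls from rises does not depend on the inference.

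Different measures for opioids and for mixed symptomatic drugs can be a deliberate choice, so the two sentences are not a contradiction. They are inconsistent in direction, and no reason is given.

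Finally, pain intensity is measured directly by ESAS-12F and the treatment list is recorded, so direction could be recovered later, and an analysis plan not shown may tabulate it. Recovery is possible, but the article fixes the outcome itself as a two-class measure. If stable was meant as no escalation, the text still needs correcting.

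**Conclusion.** The point holds in limited form. As written, the painkiller outcome pools falls and rises of more than 20% and cannot distinguish opioid sparing from opioid escalation. It can attenuate or cancel a real difference between arms and, in some scenarios, reverse it. Where comparator doses mostly rise, it keeps the right direction.

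The pooling follows from the definition alone. Its size does not: every rate and spread above is an assumption, and the p-values at 167 per arm also assume universal opioid use at baseline. Under those assumptions the stable difference ranges from 15.5 points against a sparing drug to 16.1 points in its favour, while the no-rise proportion favours the drug by 13.5 to 26.1 points throughout. It should be corrected, but it concerns one secondary outcome and leaves the primary conclusion untouched.

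**What to change.** At days 28 and 56, compare the arms on three ordered classes of change from baseline in oral morphine equivalent: fall of more than 20%, within ±20%, and rise of more than 20%. Make this the core of the outcome and report all three proportions by arm. Give the proportion with a rise of more than 20% as the directional summary, in line with the rule for other symptomatic treatments. That summary should not stand alone, since it hides movement from stable to fall.

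The protocol's 20% threshold is kept. Table 1 already schedules the treatment list at J0, J28 and J56, so no new data are needed. The cost is a short change to one secondary outcome definition and three proportions reported instead of one.

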**Discussion:**

This study will provide evidence for the pharmaceutics management of poly-symptomatology in advanced cancer patients. This could lead to important changes in the management of those patients by using a single molecule to alleviate multiple symptoms at a same time, potentially improving medication adherence, symptoms’ control, and reducing the risk of medications adverse events.

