## Background

Despite continuous progress in cancer specific treatments, cancer remains the first leading cause of death in European countries. Therefore, the scientific community has an increasing interest in improving cancer patient’s quality of life [1, 2].

Cancer patients are highly burdened by symptoms with variability depending on cancer site, stage, disease trajectory, and cancer treatments [3, 4]. This burden worsens with the disease progression. For this reason, advanced cancer patients very often experience symptoms altering their quality of life, while the aim, at this stage, is to improve it. Indeed, more than half of advanced cancer patients experience fatigue, pain, lack of energy, tiredness or lack of appetite. Unfortunately, as patients often experience multiple symptoms at the same time, they might need multiple drugs, resulting in higher risk of adverse event or drug interactions [5, 6]. A potential solution to avoid such an issue might be to use a single drug to target multiple symptoms at the same time. Additionally, very few treatments are available for some symptoms, for instance, no treatment is currently licensed in Europe for breathlessness and a very few are available for lack of appetite or loss of weight.

Mirtazapine is a licensed anti-depressive treatment, advocated to be an eligible drug in treating multiple cancer related symptoms [7, 8]. Indeed, mirtazapine has an α-2 adrenergic activity which increases noradrenergic and serotoninergic central neurotransmitters, leading to its short-term effect on acute depressive disorders [9]. Besides this α-2 adrenergic activity, mirtazapine also links to 5HT3 receptors and H1 receptors. This activity on various central and periphery receptors might have various effects on appetite, sleep disorders, pruritus, emesis, breathlessness and other multiple symptoms. Numerous recent studies gave additional clinical argument to support mirtazapine as an effective treatment for sleep disorders [10], breathlessness [11], and lack of appetite in advanced cancer patients [12].

Unfortunately, our previously published review highlighted that, despite encouraging results in various symptoms, evidence for the effectiveness of mirtazapine in improving quality of life in cancer patients experiencing poly-symptomatology is still lacking of robust randomized controlled trials [13].

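### The quantitative medication outcomes cannot show a reduction in symptomatic drugs, although substitution of several drugs by one is the trial's rationale

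*Protocol article*

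**What the plan says.** The Background of the protocol article notes that patients with several symptoms may need several drugs, and then proposes: "A potential solution to avoid such an issue might be to use a single drug to target multiple symptoms at the same time". The abstract opens with polypharmacy as a threat to quality of care and looks forward to "using a single molecule to alleviate multiple symptoms at a same time". The Discussion says of a positive result: "This could allow limiting polypharmacy in advanced cancer patients by offering a new therapeutic option well tolerated in this frail population".

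The primary objective is quality of life: "The primary objective will be to assess the effectiveness of oral mirtazapine in improving HRQoL in poly-symptomatic advanced cancer patients". Medication appears among the secondary effectiveness objectives: "The use of medications to treat associated symptoms at 28 and 56 days".

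The Outcomes assessment section turns that objective into two quantitative measures. For analgesia: "The use of painkillers will be assessed using the proportion of patients that had stable" (± 20%) oral morphine equivalent between baseline, day 28 and day 56. For all other symptomatic treatment, "the proportion of patients that increased the doses (or had new symptomatic treatment) between baseline, day 28 and day 56 will be assessed". Polymedication is also explored in semi-structured interviews, in a purposive sub-sample at the coordinating centre. Table 1 records a treatment list at J0, J28 and J56.

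**The concern.** The hoped-for benefit is that patients take fewer drugs, and the measures do not look in that direction. The flag for other symptomatic treatments is one-sided: it registers a dose increase or a new drug and nothing else. The painkiller measure is two-sided but folds both directions into one category, so a fall beyond 20% is lost among the patients who are not stable. No listed outcome counts drugs, or records a drug stopped or a non-painkiller dose lowered.

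At stake is the inference on one secondary objective. If mirtazapine works as the rationale suggests and patients drop other drugs, the stated outcomes may show no difference. If they do show one, it will concern escalation avoided, which is narrower than the claim about limiting polypharmacy.

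**Working it through.** **1. How the stated outcomes score particular patients.** This follows from the definitions and needs no assumption about rates.

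| Patient between baseline and day 56 | Net change in drugs | Flag for other symptomatic treatments |
|---|---|---|
| No change | 0 | no event |
| Stops three, starts none | −3 | no event |
| Stops three, starts one | −2 | event |
| Adds four | +4 | event |

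| Oral morphine equivalent | Painkiller outcome |
|---|---|
| Within ± 20% | stable |
| Rise of more than 20% | not stable |
| Fall of more than 20% | not stable |

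The second row of the first table is the most direct form of the hypothesised benefit, and it cannot be told apart from the first row.

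**2. The plan's own sample size.** Inputs from the Sample Size and Statistics sections: SD 26, correlation 0.5, difference 8, two-sided alpha 0.05, power 0.80, attrition 20%. SD of change = 26 × √(2 × (1 − 0.5)) = 26. The normal approximation gives 166 per group against the stated 167; power at 167 is 0.803. Then 167 / 0.8 = 208.75, so 209 per group and 418 in total. The figure reproduces and is not in dispute. I use 167 evaluable per group below.

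**3. Illustration of the lost direction (rates assumed; the protocol gives none).** Each patient starts with a Poisson number of symptomatic drugs, mean 5. Control patients add a Poisson number, mean 1.2, and stop each baseline drug with probability 0.05. The probability of at least one new drug is 1 − e^(−1.2) = 0.70.

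*More stopping only* (0.15 against 0.05; additions 1.2 in both arms):
- Flag: 0.70 against 0.70. In 4,000 simulated trials it rejects in about 5%, which is alpha.
- Mean change in count: 1.2 − 5 × 0.05 = 0.95 against 1.2 − 5 × 0.15 = 0.45, a difference of 0.50. Variances are 1.2 + 0.25 = 1.45 and 1.2 + 0.75 = 1.95. SE = √((1.45 + 1.95) / 167) = 0.143; 0.50 / 0.143 = 3.50; power ≈ Φ(3.50 − 1.96) = 0.94. Simulation agrees (94%).

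*Fewer additions only* (0.8 against 1.2; stopping 0.05 in both arms):
- Flag: 1 − e^(−0.8) = 0.55 against 0.70; simulated power 80%.
- Count: 0.55 against 0.95, a difference of 0.40; SE = √((1.05 + 1.45) / 167) = 0.122; 0.40 / 0.122 = 3.27; power ≈ Φ(1.31) = 0.90. Simulation agrees (90%).

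The flag therefore works for the effect it was built to see and has no power for the other. The 94% depends on the assumed rates. The flag's 5% does not: stopping does not enter its definition.

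**4. Does a high escalation rate defeat the flag?** At 167 per group, the smallest reduction detectable with 80% power is about 15 points at control rates of 50 to 70%, 14 points at 80% and 11 points at 90%. A deliberately extreme case: eight symptoms, each with an assumed independent 25% chance of escalation, gives 1 − 0.75^8 = 0.900. A 30% cut in each chance (to 17.5%) gives 1 − 0.825^8 = 0.785. Power for that contrast is about 82%. High rates alone do not defeat the flag.

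**The case against.** The strongest reply is that the protocol chose one of several defensible measures. The primary hypothesis is quality of life, the Discussion's statements about polypharmacy are conditional, and the per-patient proportion of improved symptoms directly tests whether one molecule relieves several. Whether fewer patients need a higher dose or a new drug is a legitimate answer to an objective worded as use of medications. The treatment lists would also let anyone derive a count later. All of this stands, and it limits the point to a secondary outcome. It does not close the gap between the stated measures and a claim of fewer drugs. In an open-label trial, a count chosen after the results are known would carry much less weight than one fixed beforehand.

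Two stronger readings are tempting and should be resisted.

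- A reader might infer from the Background's remark "This burden worsens with the disease progression" that progression will fill the flag with events in both arms and make it uninformative. Progression is balanced in expectation by randomisation, so it does not bias the comparison, and step 4 shows that a high rate does not in itself remove power. Nor does the document support a near-saturated rate: it gives no escalation rates, and eligibility requires only one under-controlled symptom besides depression.
- A reader might infer that the trial cannot address polypharmacy at all. That overlooks the escalation question, which the flag answers, the separate painkiller measure, the interviews on polymedication, and the lists from which a count can be built. The interviews explore experience at one centre, however, and do not measure drug number.

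**Conclusion.** The point holds in a limited form. The two quantitative medication outcomes cannot show a reduction: one ignores stopping and dose lowering, the other does not separate a fall from a rise. That conclusion rests only on the definitions in Outcomes assessment. Its possible size, about 5% against 94% rejection when the benefit is purely more stopping, rests on assumed figures (mean of 5 baseline drugs, 1.2 additions, stopping at 15% against 5%, 167 evaluable per group) and should be read as an illustration. The flag remains valid for escalation. The primary outcome and the sample size are unaffected. This should be corrected, but it is not a threat to the trial's main conclusion.

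**What to change.** Keep the escalation flag and add the following to the prespecified secondary outcomes:

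- Change from baseline in the number of concurrent symptomatic drugs at days 28 and 56, compared between arms, with the study drug counted separately.
- A per-patient category of net decrease, unchanged or net increase in that number.
- The painkiller outcome reported in three levels, with the existing ± 20% band: decrease, stable, increase.

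State that any conclusion about limiting polypharmacy will rest on these measures, and that a difference in the flag alone will be reported as escalation avoided.

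The cost is small. The treatment lists at J0, J28 and J56 already hold the data, so no new visit, form or patient burden is needed. Each listed drug must be classed as symptomatic or not, preferably by a rule fixed in advance and applied blind to arm, and the list of secondary outcomes grows slightly.
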